**Methods:**

We will recruit 96 participants who are willing to quit smoking by acupuncture and/or nicotine replacement therapy in Chengguan, Xigu and Heping Districts, Lanzhou city, for multicenter randomized, double-blind, double-dummy controlled clinical trial. Following obtained the informed consent forms, all eligible participants will be randomly divided into 4 groups: (1) acupuncture combined with nicotine patch, (2) acupuncture combined with sham nicotine patch, (3) sham acupuncture combined with nicotine patch, and (4) sham acupuncture combined with sham nicotine patch. These participants will be treated with different intervention modalities for 8 weeks and then will be followed-up for 8 weeks. The SPSS 26.0 software will be applied to analyze the clinical effects and adverse reactions of different intervention measures for smoking cessation.

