## Methods

### Objectives

The objective is to explore the effect and safety of different interventional approaches, e.g., acupuncture with or without nicotine patch, nicotine patch, and placebo for smoking cessation.

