### Sample size calculation

We will use the calculation formula of sample size of enumeration data in a completely random design, as describe previously. The PASS software will be used for calculation. The formula is listed as follow:$$N=\frac{\Big[{Z}_{\alpha}\sqrt{2p\left(1-p\right)}+{Z}_{\beta }{\sqrt{p_1\left(1-{p}_1\right)+{p}_2\left(1-{p}_2\right)\Big]}}^2}{{\left({p}_1-{p}_2\right)}^2}$$

*α* = 0.05 will be set up as the level of test, and the test power is 90%. The withdrawal rates of acupuncture (*p*_1_) and placebo (*p*_2_) will be 56% [18] and 9.1% [19], respectively; *p* is the mean of *p*_1_ and *p*_2_. The PASS 26.0 software will be used to calculate that the sample size required for each group for ≥18 cases. Considering 30% loss to follow-up rate, the sample size per group will be 24 cases. Consequently, the total number of the participants will be 96, based on 24 case per group in the four groups.

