### Adverse events

Adverse events in this study included needle fainting, stagnation, bending, folding, and allergy during the use of the patch, as well as adverse reactions such as bleeding, hematoma, dizziness, fainting, residual needle sensation, tenderness, and infection during the treatment. In case of any adverse reaction, the physician will take protective measures for the subject in time and decide whether to stop the trial based on the disease condition and experience director. The study director will record the time, degree, duration, and treatment measures of the occurrence on the observation sheet and indicate the date of the report, to facilitate the later evaluation of the correlation between the occurrence and the test.

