### Statistical analysis

The SPSS 26.0 software will be used for analysis. Measurement data will be expressed as *mean ± SD*, and enumeration data will be expressed as rate. Repeated measurement analysis of variance will be used for intra-group comparison of measurement data satisfying normal distribution, and SNK (Student-Newman-Keuls) method will be used for inter-group comparison; quantitative data will be tested by *χ*^*2*^. Nonparametric tests will be used for data that do not meet the normal distribution and equal variances. *P* ≤ 0.05 will be considered significant. PPS (per-protocol set) will be used in the current study, and only the data will be analyzed from the participants who will perform the whole process. For those who lack follow-up data, the data of the last observation carried forward.

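### Read literally, the completers-only rule also governs safety, so serious events and reactions that cause withdrawal would drop out of the between-arm comparison of adverse reactions

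*Protocol article*

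**What the plan says.** Safety is a stated aim. The Objectives section sets out to "explore the effect and safety of different interventional approaches", and the Methods paragraph of the Abstract says that SPSS will be used to "analyze the clinical effects and adverse reactions of different intervention measures for smoking cessation".

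The Statistical analysis section names a single analysis set: "PPS (per-protocol set) will be used in the current study". It then fixes whose records count: "only the data will be analyzed from the participants who will perform the whole process". Neither clause is limited to efficacy. The next sentence adds: "For those who lack follow-up data, the data of the last observation carried forward".

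The Dropout criteria list three events: a serious adverse event, withdrawal by the participant's own choice, and serious illness arising during treatment.

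The Adverse events section has the study director "record the time, degree, duration, and treatment measures of the occurrence on the observation sheet", so that a link to the trial can be assessed later. It does not make recording depend on completion. It names no population or denominator for comparing arms, and no exception to the completers-only rule.

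**The concern.** Whether a participant enters the analysed set depends on the outcome that the safety analysis should count. A serious event makes the participant a dropout, a dropout has not gone through the whole process, and only those who have are analysed. A milder reaction that leads someone to withdraw follows the same path.

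A harmful arm and a harmless arm could then show the same, or nearly the same, number of analysed serious events. Milder reactions would lose most cases in the arm that provokes most withdrawals. A report of few or no serious events could be read as evidence of safety when the choice of analysis set had produced it.

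This is distinct from the choice of efficacy set. An intention-to-treat rule written for abstinence alone would leave the adverse-event denominator as it is.

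**Working it through.** **Figures in the plan.** The article gives no adverse-event rate and no safety calculation, so there is no safety figure to reproduce. The arm size comes from the Sample size calculation section: 18 evaluable per group, 30% loss, 24 per group, 96 in total. The inputs there "will be 56% [18] and 9.1% [19], respectively" with 90% power give 19 per group two-sided or 16 one-sided (pooled formula, no continuity correction), close to the stated 18. The 24 matches 18 × 1.3 = 23.4, rounded up. Nothing below depends on how the 18 was obtained. The plan thus expects about 0.30 × 24 = 7.2 participants per arm, or 0.30 × 96 = 28.8 overall, to be lost.

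**Step 1: the rules side by side.** For each participant on the literal reading:

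- analysed serious event = (serious event) × (completer)
- Dropout criteria: serious event = 1 implies completer = 0
- so analysed serious events = 0, whatever the risk

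For example, assumed risks of 20%, 10%, 10% and 2% in arms of 24 give expected true cases of 4.8, 2.4, 2.4 and 0.48. The analysed counts on this reading are 0, 0, 0 and 0.

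**Step 2: how often there would be something to lose.** The serious-event risk r is assumed. Two arms sharing one active treatment hold n = 48. Expected events = n × r, and P(at least one) = 1 − (1 − r)^n.

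| Assumed risk | Expected in 48 | P(≥1) in 48 | Expected in 96 | P(≥1) in 96 |
|---|---|---|---|---|
| 1% | 0.48 | 1 − 0.99^48 = 38% | 0.96 | 62% |
| 5% | 2.4 | 1 − 0.95^48 = 91% | 4.8 | 99% |
| 10% | 4.8 | 1 − 0.90^48 = 99% | 9.6 | >99.9% |

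**Step 3: any reaction, with partial withdrawal.** Let r be the true rate of any reaction and w the fraction of those affected who withdraw, equal in both arms. Assume that other losses are unrelated to reactions. The rate among completers is r(1 − w) / (1 − rw). With r = 30% versus 10% and w = 0.5 (all assumed):

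- first arm: 0.15 / 0.85 = 17.6%
- second arm: 0.05 / 0.95 = 5.3%
- risk difference: 20 points becomes 17.6 − 5.3 = 12.3, about 12 points
- risk ratio: 30/10 = 3.0 becomes (0.15/0.85) / (0.05/0.95) = 3.35

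The limits are w = 0, where the full 20 points are kept, and w = 1, where both rates are 0. Both rates and the risk difference are understated. The risk ratio is not.

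**Step 4: does the carry-forward sentence rescue the events?** It fills in follow-up values for participants who lack them, which sits badly with analysing completers only. It does not say that participants who met a dropout criterion return to the analysis, or that their adverse events are counted. It makes the rule unclear without repairing it.

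**The case against.** The strongest reply is that the Statistical analysis section never mentions adverse events. Its methods (repeated-measures analysis of variance, SNK comparisons, carry-forward) suit the scores and abstinence outcomes. Adverse events have their own section, where recording does not depend on completion and later assessment of causality is foreseen. This stands in part: the events are not lost, and they could be listed and judged. What that section does not supply is a population for comparing arms, and the completers-only wording is addressed to the study as a whole.

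A reader might infer that zero analysed serious events in every arm is certain whatever the treatments do. The document does not support that certainty. The carry-forward sentence suggests that some non-completers may be kept. The whole process is not defined, so a participant whose event falls in the 8-week follow-up, after all treatment, might be retained. The Dropout criteria do not say that a dropout's data are discarded. The zero holds on the literal reading only.

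A reader might also infer that the reaction signal is erased, or that a powered safety test is being forfeited. Neither follows. In Step 3 the risk ratio rises slightly. With everyone counted, 5% versus 0% in 48 per side would be significant at 0.05 only with at least 6 cases by Fisher's exact test (probability about 3%), or at least 4 by uncorrected chi-square (about 22%).

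Finally, a safety set is often left to a full protocol or SAP, and its absence from an article is not a fault. That is correct, but the point rests on a study-wide rule that the article does state, and which a safety set defined elsewhere would contradict. It is also true that replacing the rule with an all-randomised one for every analysis would largely resolve this point as well.

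**Conclusion.** The point holds as a conditional one. Read literally, the completers-only rule and the Dropout criteria together take serious events, and reactions that lead to withdrawal, out of the promised between-arm analysis of adverse reactions. Analysed serious events would be zero or nearly zero at any true risk.

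The logic needs no event rate; the size does. At assumed risks of 1% to 10%, the chance that 48 participants produce at least one serious event for the rule to remove runs from 38% to 99%. The low end deserves weight: the article excludes severe heart, brain and lung disease and diabetes, and the adverse events it lists are mostly minor. For any reaction, the fall in the risk difference from 20 to about 12 points rests on assumed rates and on half of those affected withdrawing in each arm.

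Adverse events are not among the listed primary or secondary outcomes, but safety is in the objective and the article's Discussion promises a safety evaluation. Correction would give unbiased reporting of harms, not a powered comparison.

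**What to change.** In the Statistical analysis section, state that the completers-only rule does not apply to safety, and add wording such as:

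> Adverse events are analysed by arm in all randomised participants who received at least one needling session or patch, real or sham. Events that led to dropout are counted, and the denominator is all such participants.

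Report serious events and withdrawals due to adverse reactions by arm from this set, using the observation sheets already kept. In the same edit, reconcile the carry-forward sentence with the completers-only sentence.

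The Dropout criteria and the handling of reactions stay as they are. The cost is one sentence and one table, with no extra participants or data collection. The reported adverse-event rates may look less favourable.

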### Outcomes

#### Primary outcome

Abstinence rate, relapse rate, and expiratory CO value will be selected as the main outcome indexes. The former two are mainly judged by the self-report of the participants at the end of treatment and follow-up, while the expiratory CO content is mainly detected by the CO detector.

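### The only stated analysis set is per-protocol completers, so with 30% loss allowed for, the randomised comparison of abstinence is not protected

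*Protocol article*

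**What the plan says.** In the Statistical analysis section, the protocol article fixes the population: "PPS (per-protocol set) will be used in the current study". The same sentence then limits that set to completers: "only the data will be analyzed from the participants who will perform the whole process". The following sentence gives a missing-data rule: "For those who lack follow-up data, the data of the last observation carried forward". No other analysis set, and no rule that counts missing status as smoking, appears in the article.

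Three other sections bear on this:

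- **Sample size calculation:** "Considering 30% loss to follow-up rate, the sample size per group will be 24 cases".
- **Dropout criteria:** the listed reasons are serious adverse events, spontaneous withdrawal and serious disease arising during treatment. All occur after randomisation.
- **Primary outcome and Table 3:** abstinence, relapse and expired CO are all primary. Of the first two the article says "The former two are mainly judged by the self-report of the participants at the end of treatment and follow-up". Table 3 schedules abstinence at week 8 and at the end of follow-up, relapse at the end of follow-up only, and CO before treatment and at week 8.

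**The concern.** Whether someone completes is known only after randomisation, and it may depend on the treatment received or on failure to quit. Restricting the analysis to completers then compares groups that selected themselves, not the groups that were randomised.

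Two separate harms can follow. First, if those who leave are mainly smokers, abstinence among completers overstates abstinence among those randomised, even when loss is equal across arms. Second, if loss also differs between arms, completer rates can differ where the treatments do not. This rule governs the primary efficacy outcomes, and no other analysis stated in the article would reveal the problem.

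**Working it through.** **1. The plan's own sample size.** Inputs from the Sample size calculation section: the planning rates "will be 56% [18] and 9.1% [19], respectively", alpha 0.05 (taken as two-sided), power 90%, and p = (0.56 + 0.091)/2 = 0.3255. In the printed formula:

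- Z_α√(2p(1−p)) = 1.960 × √0.4391 = 1.299
- Z_β√(p₁(1−p₁) + p₂(1−p₂)) = 1.282 × √0.3291 = 0.735
- N = (1.299 + 0.735)² / 0.469² = 18.8, so 19

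The article states "the sample size required for each group for ≥18 cases", which is close. Its 24 per group follows from 18 × 1.3 = 23.4.

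**2. Who leaves the analysis.** At 30% loss, 0.30 × 24 = 7.2 per group and 0.30 × 96 = 28.8 in total are excluded. About 17 per group remain. Power at 17 per group with the planning rates is 87%.

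**3. Overstatement of abstinence.** Assume that everyone lost is a smoker. The completer rate is then the rate among all randomised divided by 0.70, a factor of 1.43.

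- If 56% and 9.1% describe all randomised, completers show 0.56/0.70 = 80% and 0.091/0.70 = 13%.
- If 56% and 9.1% describe completers, the rates among all randomised are 0.56 × 0.70 = 39.2% and 0.091 × 0.70 = 6.4%.

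**4. False-positive risk.** Simulation of two arms of 24 with true abstinence of 25% in both, only smokers lost, and an uncorrected chi-square test at 5%. The apparent rate in each arm is 0.25/(1 − loss).

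| Loss in the two arms | Apparent abstinence | Rejection rate, completers only |
|---|---|---|
| 30% / 30% | 36% / 36% | about 5.3% |
| 35% / 25% | 38% / 33% | 6.4% |
| 40% / 20% | 42% / 31% | about 10% |
| 45% / 15% | 45% / 29% | about 17% |
| 50% / 10% | 50% / 28% | about 26% |

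With all randomised participants analysed and missing counted as smoking, the rejection rate is about 5.3% in these scenarios. With a continuity-corrected test, the 40/20 completer figure falls to 4.8%. The loss splits and the 25% are assumptions; the article gives only the overall 30%.

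**5. What carrying forward can and cannot do.** Abstinence is first recorded at week 8. Someone who leaves before then has no abstinence value to carry, so the rule cannot restore them. Someone lost after week 8 does have a value. If they had quit at week 8, they would be counted as abstinent at the end of follow-up, and any relapse would be hidden. Relapse is itself a primary outcome.

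**The case against.** The strongest defence is that the two sentences can be read together. Treatment and follow-up are separate 8-week periods. Completing the process may mean completing treatment, with carry-forward applied only to treatment completers who miss the follow-up visit. A reader might infer that the article defines two incompatible populations, but the text does not establish that: it is ambiguous and needs reconciling. On the milder reading, people lost after week 8 stay in the denominator, but with the hidden-relapse problem shown above. People lost during treatment are still excluded.

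Three other strong readings are not supported:

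- **That randomisation is broken, or a false positive assured.** With equal loss the error rate stays near 5%, and at 35/25 it is only 6.4%. What is lost is the protection.
- **That abstinence is necessarily inflated in every arm.** This requires those lost to be abstinent less often. The article gives no data on that, and its dropout reasons include serious adverse events and serious disease.
- **That the burden of needling sessions drives unequal loss.** The design is double-dummy, and one session schedule, 3 × 4 + 2 × 4 = 20, applies to all four arms. Unequal loss could come from reactions to real versus sham treatment, or from practitioners whom the article admits it cannot blind. Blinded participants and online data collection reduce this risk but do not remove it.

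A separate analysis plan may exist. That does not answer the point, because the article makes an explicit choice of population.

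**Conclusion.** The point stands and should be corrected before analysis. The article restricts its only stated analysis to completers while allowing for 30% loss, and the carry-forward sentence cannot bring back anyone lost before week 8.

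The size depends on facts the article does not give. The overstatement of abstinence reaches 1.43 times only if every person lost is a smoker. The false-positive risk ranges from near 5% with equal loss to about 26% at a 50/10 split, under the assumptions in the working. The claim is therefore that the randomised comparison is left unprotected on the primary efficacy outcomes, not that bias of a particular size will occur.

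**What to change.** Replace the last two sentences of the Statistical analysis section with rules to this effect:

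- **Population:** the primary efficacy analysis includes all randomised participants in their assigned group.
- **Abstinence:** missing status at week 8 or at the end of follow-up counts as smoking.
- **Relapse:** defined among those abstinent at week 8, with a missing follow-up record counted as relapse.
- **CO:** week-8 CO analysed in all randomised participants with available data, adjusted for baseline CO, with a sensitivity analysis for missing values. Counting missing as smoking cannot supply a continuous reading, so CO needs its own rule.
- **Carry-forward:** dropped for abstinence and relapse.
- **Per-protocol set:** kept as a sensitivity analysis, with "the whole process" defined so that it is clear whether follow-up is included.

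The change is to wording, but it has consequences. Reported abstinence will be lower wherever people are lost. Power should be restated. If 56% and 9.1% refer to completers and everyone lost smokes, the rates among all randomised are 39.2% and 6.4%. Power at 24 per group is then about 79%, and 33 per group would be needed for 90%. If the planning rates already refer to all randomised, power at 24 per group is about 96%. The sponsor should say which applies.

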### Blinding

In this study, a randomized, controlled, double-blind, double-dummy, multi-center experimental design method will be adopted. In view of the particularity of acupuncture manipulation, it is difficult to blind the practitioners of the study. Thus, we can only blind the participants and the data collectors. The specific operation process is as follows: prior to the study, the participants will sign the informed consent, and each participant will be informed that both acupuncture and patch treatment methods would be adopted. The research group will select two groups of acupuncture points (Fig. 2, Fig. 3), so the locations of each acupuncture point may be different, but we will not inform the specific names of the acupuncture points and their effects. Because placebo patches are the exact size and shape of the patch that has already been purchased, the participants will be masked the intervention received all the time. In addition, in our data collection process, specialized data collectors send questionnaires to the research objects in the form of “Questionnaire Star,” and the data collection is completed through the network. To ensure the correct application of blindness in this study, these participants will be not aware of the grouping of the research objects.

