#### Secondary outcome

Secondary measures included a modified Fagerstrom test for nicotine dependence (FTND) score, a Minnesota Nicotine Withdrawal Scale (MNWS), and modified Brief Questionnaire of Smoking Urge (QSU-Brief) score. The three scores will be used to reflect the severity of nicotine dependence, withdrawal symptoms, and smoking craving of the participants. The higher scores indicate, the more severe symptoms. Each patient will be asked a questionnaire prior to the treatment and at 1, 4, and 8 weeks after the treatment. Table 3 shows the specific observation points of each index during the study.

**Table 3 Tab3:** The measurement time points of various indicators

Indicators	Before start of treatment	Treatment period			End of the follow-up
		Week 1	Week 4	Week 8	
Abstinence rate				√	√
Relapse rate					√
Expiratory CO value	√			√	
FTND scores	√	√	√	√	
MNWS	√	√	√	√	
QSU-Brief scores	√	√	√	√	

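### The only analysis set is completers, so randomised dropouts leave the abstinence comparison, and the carry-forward rule neither fits with this nor repairs it

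*Protocol article*

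**What the plan says.** All references are to the protocol article.

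- **Analysis set** (Statistical analysis): "PPS (per-protocol set) will be used in the current study". The same sentence then limits this set to completers: "only the data will be analyzed from the participants who will perform the whole process". No intention-to-treat or full analysis set appears anywhere in the article.
- **Missing data** (same section, next sentence): "For those who lack follow-up data, the data of the last observation carried forward".
- **Outcomes** (Primary outcome): abstinence, relapse and expiratory CO are the main outcomes. Of abstinence and relapse it says: "The former two are mainly judged by the self-report of the participants at the end of treatment and follow-up".
- **Timing** (Secondary outcome, Table 3): abstinence is marked at week 8 and at the end of follow-up only, and relapse at the end of follow-up only. FTND, MNWS and QSU-Brief also have baseline, week-1 and week-4 values.
- **Dropout criteria**: serious adverse events, spontaneous withdrawal, and serious disease arising during treatment.
- **Expected loss** (Sample size calculation): "Considering 30% loss to follow-up rate, the sample size per group will be 24 cases".

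**The concern.** Every listed reason for dropout arises after randomisation, and each could depend on the treatment received or on failing to quit. If such participants are removed, the groups compared are no longer the groups that were randomised. A difference in abstinence can then be created or hidden wherever dropout differs between arms.

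Unblinded staff add a possible route. After an adverse reaction the physician may "decide whether to stop the trial based on the disease condition and experience director", and the Blinding section concedes that "it is difficult to blind the practitioners of the study". If stopping here means stopping for that participant, which is an interpretation, someone who knows the arm can influence who remains in the analysis. The argument does not need this, because the dropout criteria suffice.

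The set also does not suit the stated purpose. The abstract calls the trial pragmatic, and the Discussion wants to help smokers choose a programme. That choice needs the result for everyone assigned to a treatment, not only for those who finished it. Encouragement to stay in (Participant's management system) and adverse-event records (Adverse events) are useful, but neither brings dropouts back into the comparison.

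**Working it through.** **1. The two sentences side by side.** The article does not define the whole process, so there are two readings.

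- *Reading A: it includes follow-up.* Someone lost to follow-up has not completed and is already excluded, so the carry-forward rule has essentially nobody to act on.
- *Reading B: it means the 8 treatment weeks.* Someone abstinent at week 8 and then lost has abstinence carried to the end of follow-up. That person counts as not relapsed across the very period in which relapse is measured. Relapse within an arm is then either right or understated, never overstated.

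Under neither reading is a participant stopped before week 8 counted, and Table 3 schedules no earlier abstinence value to carry. Entrants are daily nicotine users (Diagnostic criteria), so baseline status could have been carried forward as not abstinent. The section does not say so, and the completers rule removes these participants first. This point concerns abstinence and relapse only, because the three scales do have earlier values.

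**2. The plan's own figures.** Inputs from Sample size calculation: p1 = 0.56, p2 = 0.091, alpha 0.05, power 90%, 30% loss. The printed formula gives 18.8, so 19 per group two-sided, or 15.1, so 16 one-sided, against the stated 18. Then 18 × 1.3 = 23.4, rounded up to 24, and 4 × 24 = 96. These figures reproduce closely enough for the present purpose.

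**3. How many could leave.** One participant is 1/24 = 4.2% of an arm. The planned loss is 0.30 × 24 = 7.2 per arm, or 0.30 × 96 = 28.8 in total. This is a planning allowance, used here only as the upper end of the range.

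**4. Inflation within an arm.** With k lost and none of them abstinent (assumed), the completers' rate is the all-randomised rate × 24/(24 − k):

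| k | 0 | 1 | 2 | 3 | 4 | 5 | 6 | 7 |
|---|---|---|---|---|---|---|---|---|
| Factor | 1.00 | 1.04 | 1.09 | 1.14 | 1.20 | 1.26 | 1.33 | 1.41 |

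**5. False gap with no true effect.** Assume 6/24 = 25% abstinent in both arms, with k lost from one arm and none from the other.

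- k = 0: no gap.
- k = 4: 6/20 = 30.0%, a gap of 5.0 points.
- k = 7: 6/17 = 35.3%, a gap of 10.3 points.

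**6. Equal loss.** Take the planned 56% and 9.1% as abstinence rates that hold among 17 completers per arm, with 7 lost per arm and none abstinent (assumed).

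- Completers only: 56.0 − 9.1 = 46.9 points.
- All randomised: 0.56 × 17/24 = 39.7% and 0.091 × 17/24 = 6.4%, a gap of 0.469 × 17/24 = 33.2 points.

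**7. Relapse under reading B.** 0.56 × 24 = 13.4, so take 13 abstinent at week 8. Let j be lost afterwards, up to 4 (30% of 13 = 3.9), and assume 50% relapse among the rest.

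| j | Carried forward: 0.5(13 − j)/13 | Lost counted as relapsed: [0.5(13 − j) + j]/13 |
|---|---|---|
| 0 | 50.0% | 50.0% |
| 2 | 42.3% | 57.7% |
| 4 | 34.6% | 65.4% |

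**The case against.** The strongest reply accepts the completers-only rule as stated and contests what is built on it.

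- **Conflict or ambiguity?** Reading B reconciles the two sentences, and the abstract does separate 8 weeks of treatment from 8 weeks of follow-up. Someone could also attend every session and leave an online questionnaire unanswered, so reading A may leave a few people to carry forward. This is fair, but the article does not say which reading it intends, and treatment-phase dropouts are excluded under both.
- **Relapse is an inference.** Table 3 gives relapse no value before the end of follow-up, so the rule does not literally carry a relapse status. True, but carrying week-8 abstinence forward implies no relapse. The 50% relapse rate is assumed.
- **The sizes are possibilities.** The 10.3-point gap needs all the loss in one arm and no quitters among the lost, and the plan gives one loss rate for every arm. At 6/17 against 6/24 an uncorrected chi-square gives p of about 0.48, so this example would not be declared significant. In the equal-loss example the ratio of the two rates does not change; what changes is the quantity estimated. Under a true null, equal loss creates no false gap. All of this stands and limits the claim to what could happen.
- **The planned rates.** The article labels 56% and 9.1% as withdrawal rates, and does not say whether they come from completers or from all participants. Their use here is an assumption.
- **The remedy imputes too.** Counting all lost week-8 abstainers as relapsed is the opposite extreme from carry-forward. This stands, and it is why a sensitivity analysis belongs with the change.

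**Conclusion.** The point holds. The article does not leave the analysis set open: it fixes completers only, for main outcomes, in a trial that plans for 30% loss. The carry-forward sentence either has almost nobody to apply to or understates relapse, and it never restores those stopped before week 8.

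The size and between-arm direction of the bias cannot be derived from the document. The illustrative ranges are a 1.00 to 1.41-fold inflation of one arm's abstinence rate, a false gap of 0 to 10.3 points, and at the extreme a relapse rate shown as 34.6% where counting the lost as relapsed gives 65.4%. They rest on the assumed rates shown and on up to 30% loss; the abstinence figures also assume that no dropout quits. If those lost quit at the same rate as the rest, there is no bias. The section should be corrected before analysis; the design need not change.

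**What to change.** In Statistical analysis:

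1. Make all randomised participants, in their assigned groups, the main set for abstinence at week 8 and at the end of follow-up.
2. Count those with no answer at a time point as not abstinent, and week-8 abstainers with no answer at the end of follow-up as relapsed. Drop carry-forward for abstinence and relapse.
3. Keep the per-protocol set as secondary.
4. Add a sensitivity analysis that varies the non-responders' quit rate from 0 to the rate among responders in their own arm. Do the same for relapse, from all of the lost relapsed down to the responders' relapse rate.

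To support this, state under Dropout criteria that stopping needles or patch does not end data collection. Send the week-8 and end-of-follow-up self-report questions to everyone who has not withdrawn consent. The data already come in over WeChat, so this is feasible.

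**Cost.** The change needs new wording and a few more online questionnaires, some of which will go unanswered. Expiratory CO stays missing for those who do not attend. The main result will describe assignment to a treatment, not completion of it. Counting non-responders as smoking can itself mislead if some have quit and non-response differs by arm.

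Some power is lost. With 7 of 24 lost per arm and none abstinent (assumed), full binomial enumeration for one pairwise uncorrected chi-square test at 0.05 gives 84% (24 per arm, 39.7% v 6.4%), against 87% for completers only (17 per arm, 56% v 9.1%). A normal approximation gives about 80% against 87%, so the loss is roughly 3 to 7 points.
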